## Methods and analysis

### General design

PHOENIX is a two-centre, mixed methods, feasibility RCT with 1:1 randomisation into either intervention or usual care. The trial will be open to recruitment between 1 May 2024 and 31 January 2025. Qualitative interviews will be conducted with participants in the intervention arm and staff involved in delivering the intervention. The trial is being conducted in accordance with the principles of the Declaration of Helsinki and good clinical practice (GCP).

### Participants, interventions and outcomes

#### Study setting

This study is being undertaken in two general adult UK ICUs (University Hospital Coventry and Warwickshire, Coventry and John Radcliffe Hospital, Oxford) which have a proven track record in ICU research.

### Eligibility criteria

Written informed consent is obtained from participants prior to any study procedures taking place (online supplemental file 1). Eligible patients with altered consciousness caused by illness and therapeutic sedation will lack capacity to consent. In this instance, we will approach a personal consultee or an independent registered medical practitioner if no personal consultee is available. Once the participant has recovered from their incapacity, they will be approached to obtain permission to continue in the study. Patients eligible for the study must comply with all of the following before randomisation:

Adults (≥18 years) who received ≥4 days advanced respiratory support (defined as invasive or non-invasive ventilation) within ICU.Alive at ICU discharge.Ongoing physiotherapy and dietetic rehabilitation needs identified by the Post-ICU Presentation Screen tool (defined as patients who are unable to transfer from bed to chair independently and not able to meet nutritional requirements independently).

Patients are excluded if they meet any of the following criteria:

Death expected within the next 72 hours.Poor pre-ICU admission mobility (inability to walk>10 m with or without an aid).Mobilisation contraindicated (eg, spinal injury).Contraindication to or inability to tolerate enteral nutrition.Significant acquired brain injury and not recovered to a Glasgow Coma Scale score of ≥14 by ICU discharge.

The inclusion and exclusion criteria are designed to include participants who reflect a general population of patients that have ongoing physical rehabilitation and nutritional needs on discharge from ICU and exclude patients who are unable to mobilise.

### Intervention

The intervention consists of a combination of structured, individualised physiotherapy and optimised nutrition, beginning immediately following recruitment and continuing for up to 14-days or hospital discharge, whichever is sooner. The physiotherapy or nutritional intervention will be terminated early if no longer deemed to be clinically required or appropriate (eg, patent deterioration and receiving end-of-life care; enteral nutrition becomes contraindicated).

The enhanced physiotherapy intervention will be delivered by a dedicated team led by a physiotherapist. The intervention comprises (1) completion of a comprehensive physical and non-physical assessment to create an individualised treatment plan, (2) setting of patient-centred rehabilitation goals with regular reassessment, (3) provision of daily physiotherapy (Monday–Friday), targeting the highest level of mobility attainable and delivery of individualised exercise programmes and (4) close working with ward staff to optimise treatment delivery and ensure seamless transitions of care once the enhanced intervention is complete.

The nutritional component will be led by a specialist dietitian. A comprehensive nutritional assessment will be completed on day one of the intervention period to include current nutritional intake from oral diet, nutritional supplements and enteral tube feeding. Indirect calorimetry (QNRG+) will be used where possible to determine resting energy expenditure, and protein requirements will be calculated using weight-based equations. An individualised nutritional plan will be devised, to include dietary modification, additional food provision, prescription of oral nutritional supplements or modification to enteral feeding regimen as required. This may also include prescribed nutritional supplementation used within 2 hours of the physiotherapy session to address the catabolic nature of exercise. Review and adjustment to the nutritional care plan will occur daily (Monday–Friday) throughout the intervention period. At the end of the intervention period, patients will be transferred to standard dietetic care, with a comprehensive handover provided.

### Usual care

Usual care consists of routine ward-based care including standard dietetic care, mobilisation and rehabilitation interventions, which may include activities of daily living, delivered during normal working hours (between 08:00 and 17:00, Monday–Friday). No further input or involvement will be provided from ICU therapy teams.

### Participant and staff interviews

Semistructured interviews to assess intervention acceptability will be undertaken with a subset of participants in the intervention arm. We will purposively sample participants to ensure a range of age, sex and reason for ICU admission. Participants will be interviewed at a time convenient to them after discharge from hospital. We will also interview staff from the multidisciplinary team that were involved with the delivery of the intervention. Staff may be interviewed at any time during, or shortly after, the intervention period at their site. All interviews will follow a topic guide developed and piloted with input from the patient contributors. The interview content will aim to explore the participants’ and providers’ experiences of receiving and delivering the intervention, barriers to engagement or delivery, and ideas for improving the intervention. It is envisaged that interviews will take up to 45 min.

### Participant timeline

Participant timeline is shown in figure 1.

**Figure 1 F1:**
[figure not shown]
Flow of participants through the study. ICU, intensive care unit; EQ5D-5L, 5 level EQ5D version; MMS, Manchester Mobility Score; MODRUM, Modular Resource Use Measure.

### Outcome measures

#### Primary outcome measures

Recruitment rate, overall and by centre.Retention rate, defined as the proportion of participants that complete the primary outcome.Intervention adherence measured by the proportion of enhanced physiotherapy sessions completed and nutrition delivery compared with targets.Acceptability of the intervention to participants and service providers.

#### Secondary outcome measures

Measures that will be used in the future full-scale trial will also be collected at baseline, 14 days or hospital discharge (whichever comes sooner) and at 30 and 90 days following randomisation. The proposed primary outcome for the definitive RCT will be days alive and out of hospital (DAOH) within 30 days. Out of hospital is classified as being at home or usual residence and defined as 30 minus the number of days in hospital (range 0–30), with 0 assigned for death within the 30 days. DAOH is a patient-centred outcome, has been validated with a range of clinical specialties^29^ and takes account of those patients who die or are discharged to community rehabilitation settings.

Further secondary outcomes include:

Physical function (30 s sit to stand test).Functional independence (Barthel Index).Quality of Life (EQ-5D-5L).

Additional outcomes collected are:

DAOH at 90 days.Hospital-acquired malnutrition (Global Leadership Initiative on Malnutrition - GLIM criteria).Weight and percentage change in weight.Time to complete therapy.Hospital discharge destination.Anthropometric measurements (mid-arm circumference, triceps skin fold, hand grip).

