Proportion of patients agreeing to take part out of all those invited (recruitment rate).Proportion of participants who complete the intervention (retention rate).Percentage of intervention sessions completed (intervention fidelity).Intervention acceptability to participants and service providers.

The secondary objectives are

To evaluate a range of clinical and patient-reported outcome measures to aid selection of the most appropriate primary outcome measure for a definitive trial, with estimates for sample size calculation and health economic evaluations of any future definitive trial.

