**Figure 2 F2:**
[figure not shown]
Consolidated Standards of Reporting Trials pilot and feasibility trials flow schematic. PHOENIX, Physiotherapy and Optimised Enteral Nutrition In the post-acute phase of critical illness.

**Table 1 T1:** Timing of visits and data collection

Baseline (pre randomisation)	Confirmation with inclusion and exclusion criteriaDate and time of consentPatient demographics (age, sex, ethnicity, height, weight)Relevant clinical history (depression, anxiety, comorbidities)Primary admission diagnosisICU length of stayDuration of sedationDuration of mechanical ventilationMMSWeightHospital Malnutrition Score (GLIM criteria)Barthel IndexHand grip strengthMid-arm circumference/triceps skin fold30 s sit to stand
Daily for 14 days or until hospital discharge	Frequency and level of mobilisation (MMS)Nutrition and calories consumedTherapy contacts and durationMobilisation-related complications
End of intervention/hospital discharge	WeightBarthel indexEQ-5D-5LHand grip strength30 s sit to standPost-ICU length of staySemistructured interviewsMortality
30 days post randomisation	WeightEQ-5D-5LGrip strengthMid-arm circumference/triceps skin fold30 s sit to standMortalityResource use (MODRUM)Return to work or normal activity
90 days post randomisation	MortalityResource use (MODRUM)Return to work or normal activity

EQ5D-5L5 level EQ5D versionGLIMGlobal leadership initiative on malnutritionICUintensive care unitMMSManchester Mobility ScoreMODRUMModular Resource Use Measure

In addition to the primary outcome of DAOH, we propose to collect several secondary measures at 30 days and 90 days for evaluation. To enable this, where possible the 30-day and 90-day assessments will be completed face to face in a hospital clinic, if the participants have an appointment scheduled. If this is not possible due to the participant being out of area, unable to travel to the hospital or an appointment is not scheduled, components of the assessment identified will be completed via telephone or video conferencing (outlined in table 1).

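### Function at the day 14/discharge visit is timed by discharge and is not a fixed-time estimate; in Table 1 the Barthel Index has no other follow-up, contrary to the text

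*Protocol article*

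**What the plan says.** The Secondary outcome measures section says that the measures intended for the full-scale trial "will also be collected at baseline, 14 days or hospital discharge (whichever comes sooner) and at 30 and 90 days following randomisation". Sit to stand, Barthel Index and EQ-5D-5L are then named as further secondary outcomes.

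Table 1 (Data collection) gives the detailed schedule:

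- End of intervention/hospital discharge: "WeightBarthel indexEQ-5D-5LHand grip strength30 s sit to standPost-ICU length of staySemistructured interviewsMortality".
- Day 30: "WeightEQ-5D-5LGrip strengthMid-arm circumference/triceps skin fold30 s sit to standMortalityResource use (MODRUM)Return to work or normal activity".
- Day 90: "MortalityResource use (MODRUM)Return to work or normal activity".

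On the later visits, the text below Table 1 says that "where possible the 30-day and 90-day assessments will be completed face to face in a hospital clinic, if the participants have an appointment scheduled"; otherwise, components are done by telephone or video.

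The secondary objective is to help choose the definitive trial's primary outcome, "with estimates for sample size calculation and health economic evaluations of any future definitive trial". The proposed primary outcome for that trial is DAOH within 30 days. Data analysis plans descriptive summaries: means, ranges, SDs and CIs.

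**The concern.** A visit held at the earlier of day 14 and discharge happens when the patient is judged fit to leave, or at day 14 if that comes first. The article itself links leaving hospital to function: the Introduction says that patients unable to stand before ICU discharge stay longer in hospital. The choice of DAOH as proposed primary outcome presumes that treatment may shorten the stay. If the intervention speeds recovery, its patients may be measured after fewer days, at about the functional level needed for discharge. Both the between-arm difference and the SD may then be smaller than at a common day.

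At stake is the use of these data to compare candidate outcomes and to supply sample-size inputs. For Barthel the schedule in Table 1 leaves no alternative source, and no later analysis can recover a fixed-time score that was not collected.

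**Working it through.** **1. Table 1 against the text.** The text promises the measures at days 30 and 90.

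| Measure | End of intervention/discharge | Day 30 | Day 90 |
|---|---|---|---|
| Barthel Index | yes | no | no |
| 30 s sit to stand | yes | yes | no |
| Grip strength | yes | yes | no |
| EQ-5D-5L | yes | yes | no |

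Barthel is the only one of the four without a fixed-time follow-up. None of the four is listed at day 90.

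**2. Figures in the plan.** There is none to reproduce. The article gives no functional SD, effect, length-of-stay distribution or discharge criterion. Every input below is an assumption, chosen only to show direction and range.

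**3. Illustration: discharge driven by function.** Score of patient i on day t: Y_i(t) = b_i + s_i·t. Discharge day T_i is when the score reaches the patient's threshold; the visit is at A_i = min(T_i, 14). Assumed: baseline mean 30, SD 12; control gain 1.0 to 3.0 points/day, SD 0.8; gain 25% faster on intervention; threshold mean 60, SD 10; measurement error SD 5; 400,000 simulated patients per arm.

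| Control gain/day | Difference at visit | Difference at fixed day 14 | Share seen | SD at visit | SD at fixed day 14 |
|---|---|---|---|---|---|
| 1.0 | 2.31 | 3.71 | 62% | 14.5 | 17.4 |
| 1.5 | 2.69 | 5.31 | 51% | 13.6 | 17.9 |
| 2.0 | 2.64 | 7.01 | 38% | 12.4 | 18.1 |
| 3.0 | 1.62 | 10.49 | 15% | 10.9 | 18.2 |

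A second set of assumptions (gain 2-3 points/day, SD 1.2; 20-25% faster; threshold 50 to 80) gave 19-84%. I repeated it: 15-75% with scores bounded at 0 and 100, and 11-69% without bounds. The limits of the range are therefore indicative only.

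**4. Consequence for sample size.** For two means at two-sided 0.05 and 90% power, n per arm = 2(1.960 + 1.282)²(SD/difference)².

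- SD from the visit combined with a target difference set for a fixed time: n is multiplied by (SD at visit / SD at day 14)². This is (14.47/17.37)² = 0.69 for the slowest recovery and (10.89/18.17)² = 0.36 for the fastest, so n is 31% to 64% too small.
- Difference and SD both from the visit: n per arm is 823, 537, 465 and 952 in the four rows, against 460, 240, 141 and 64 at a fixed day 14.

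**5. Illustration: discharge independent of function.** With length of stay drawn separately (mean 14, SD 6 days), the share seen is about 83% in all four rows (for example 2.98/3.57 and 8.77/10.55). The SD is 0.96 to 1.08 times the fixed-time SD.

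**6. Sampling error in this trial.** With 30 per arm and an SD of 19, the 95% half-width for a difference is 1.96 × 19 × √(2/30) = 9.6 points. One illustrative case in the second set of assumptions showed 2.7 points at the visit against 6.5 at day 14, a gap of 3.8.

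**The case against.** The visit coincides with the end of an intervention that runs "beginning immediately following recruitment and continuing for up to 14-days or hospital discharge, whichever is sooner". Function at the end of treatment is a legitimate quantity, and Table 1 names the visit for that, not as day 14. If the definitive trial keeps the same visit, its SD is the right input. All this stands.

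A reader might infer that this is the trial's main functional assessment and that its planning estimates for function are distorted as a whole. The documents do not support that. No functional time point is ranked first, and nothing says sample-size inputs will come from this visit. DAOH-30 has a fixed window that this visit does not touch. Sit to stand, grip strength and EQ-5D-5L have a fixed day-30 assessment. That safeguard is only partial for the physical tests, because a remote day-30 visit may leave them missing.

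The size is also open. Slow recovery is plausible in patients who cannot transfer to a chair unaided at entry: at 1 point/day with a threshold of 80, about 81% of the difference is seen. Some discharges will be to community rehabilitation, so function is not their only driver. With a descriptive analysis and about 30 per arm, sampling error exceeds the illustrative bias (step 6).

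Reporting the assessment day by arm could be left to a statistical analysis plan, so its absence is not an error. The Barthel gap does not fall away in this manner: the article states a detailed schedule that disagrees with its own text. The figures and the full protocol are not at hand and may list Barthel later, but the two published statements would still need reconciling.

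**Conclusion.** The point holds in limited form. Data from the day 14/discharge visit are end-of-intervention descriptions at a time that depends on discharge; they are not fixed-time estimates and can mislead if used as such. For Barthel, Table 1 offers nothing else, although the text says the measures are also collected at 30 and 90 days.

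The size cannot be determined from the documents. The range of roughly 15-84% of a fixed day-14 difference rests wholly on assumed recovery rates and function-driven discharge; about 83% applies if discharge is unrelated to function. The feasibility outcomes and DAOH-30 are not affected. This is a cheap improvement to make, not a flaw that undermines the trial.

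**What to change.** - Add the Barthel Index to the day-30 contact in Table 1 for all participants, in the same way in both arms, by telephone where needed. Telephoning only those already discharged at day 14 would be worse, because the mode of assessment would then depend on discharge.
- Reconcile Table 1 with the Secondary outcome measures section on what is collected at day 90.
- Take the outcome-selection comparison and sample-size inputs for function and EQ-5D-5L from day 30, unless the definitive trial will use the same end-of-intervention visit.
- Report the actual day of the in-hospital assessment, counted from randomisation, by arm.

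The cost is a few minutes at an existing contact and some wording. The drawback is that sit to stand and grip strength will be missing for some participants seen remotely at day 30; that proportion should be reported alongside the estimates.

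### The DAOH formula subtracts only hospital days, while the same sentence counts only days at home or usual residence, so survivors with days in non-hospital rehabilitation get two different scores

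*Protocol article*

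**What the plan says.** The definition is in the protocol article under Secondary outcome measures. DAOH is put forward for the next trial: "The proposed primary outcome for the definitive RCT will be days alive and out of hospital (DAOH) within 30 days". The scoring sentence begins: "Out of hospital is classified as being at home or usual residence and defined as 30 minus the number of days in hospital". With what follows, it has three parts:

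- a location rule, under which only days at home or usual residence count;
- a formula, which takes hospital days from 30, with a stated range of 0–30;
- a death rule: "with 0 assigned for death within the 30 days".

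The following sentence says that the measure "takes account of those patients who die or are discharged to community rehabilitation settings". The article does not say how a day in such a setting is scored, or whether the unit counts as hospital. DAOH at 90 days is listed as an additional outcome without a definition of its own. "Hospital discharge destination" is also listed there, as a separate outcome.

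Under Data analysis, the distributions of DAOH-30 and DAOH-90 are to guide the choice of analysis model and the planning of the definitive trial. In Table 2, retention is judged by whether DAOH was collected.

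**The concern.** The location rule and the formula treat a third kind of day differently: a day in neither an acute hospital nor the participant's home. The location rule gives no credit for it. The formula gives full credit, because it subtracts only hospital days.

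Such days are to be expected here. Participants must be unable to transfer from bed to chair independently at ICU discharge. The Introduction says that the most debilitated patients are more likely to need continuing rehabilitation after leaving hospital. The article itself names discharge to community rehabilitation as something the outcome should reflect.

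What is at stake is the planning information. The mean, the spread and the proportion of zeros of DAOH-30 are what a definitive trial would be built on, and all three depend on which rule is applied. Two people deriving the variable from the same records could both follow the text and obtain different values.

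**Working it through.** **Inputs.** The location rule, formula, death rule and range come from Secondary outcome measures. The numbers of days in the examples are my assumptions, since the article gives none.

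**Notation.** For a participant alive at day 30, let h be the days in hospital and r the days in a non-hospital rehabilitation or other temporary care setting, both within the 30 days.

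- Formula as written: 30 − h
- Location rule: 30 − h − r
- Death by day 30: 0 under both
- Difference for a survivor: (30 − h) − (30 − h − r) = r

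**The article's own figure.** Both rules reproduce the stated range of 0–30: h = 0 and r = 0 gives 30, and h = 30 gives 0. The range therefore does not show which rule is meant.

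**Examples.**

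| h | r | Status at day 30 | Formula | Location rule | Difference |
|---|---|---|---|---|---|
| 14 | 0 | alive | 30 − 14 = 16 | 30 − 14 − 0 = 16 | 0 |
| 14 | 7 | alive | 30 − 14 = 16 | 30 − 14 − 7 = 9 | 7 |
| 10 | 14 | alive | 30 − 10 = 20 | 30 − 10 − 14 = 6 | 14 |
| 14 | 16 | alive | 30 − 14 = 16 | 30 − 14 − 16 = 0 | 16 |
| 14 | 10 | dead | 0 | 0 | 0 |

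The fourth row bears on the choice of model. Under the location rule a survivor can score 0 and join the deaths. Under the formula the same person scores 16.

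**Effect on a mean.** If a proportion p of participants are survivors with an average of r such days, the two means differ by p × r. With r = 14:

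- p = 0.10: 0.10 × 14 = 1.4 days
- p = 0.25: 0.25 × 14 = 3.5 days

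A wider set of assumptions, p from 0.10 to 0.30 and r from 7 to 16, gives 0.10 × 7 = 0.7 to 0.30 × 16 = 4.8 days.

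**Which rule fits the rest of the text.** The statement about community rehabilitation holds under the location rule, where those days lower the score. It fails under the formula taken literally, where they score the same as days at home. It could hold under the formula only if community rehabilitation counted as hospital, and the article does not say that.

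**The case against.** The best defence is that the intent can be read from the text. Out of hospital is first tied to home or usual residence, so days in hospital can be taken as everything else, and the rehabilitation sentence supports that reading. This stands as an account of what was probably meant. It does not rescue the formula, which still gives the wrong score when applied as written.

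DAOH is also a secondary outcome here, analysed descriptively, and choosing the definitive primary outcome is itself an aim of the study. That limits the harm to planning, and no treatment comparison in this trial depends on it.

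A reader might infer four stronger things that the article does not support:

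- *Every participant discharged to rehabilitation is mis-scored.* The rules agree for deaths by day 30, for transfers to rehabilitation after day 30, and where the unit counts as hospital.
- *The data for the home-based version are not collected.* Table 1 does not itemise dates of changes of setting, and its 90-day row reads "MortalityResource use (MODRUM)Return to work or normal activity". But discharge destination is a listed outcome, the resource-use questionnaire is given at 30 and 90 days, and Feasibility economic evaluation plans to track patients through the system for 90 days. A condensed article does not show the case report form fields, so their absence cannot be concluded.
- *The retention criterion is undermined.* Table 2 asks whether DAOH was collected, which does not depend on how a rehabilitation day is scored.
- *The direction of effect would reverse.* It is possible to construct such a case. With 10 hospital and 14 rehabilitation days in one arm against 16 hospital days and then home in the other, the formula gives 20 against 14 and the location rule 6 against 14. Those figures are invented, and nothing in the article says that destinations will differ by arm in this way.

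**Conclusion.** The definition is wrong as written. For survivors, the formula and the location rule differ by exactly the number of days within the window spent in non-hospital rehabilitation or other temporary care. That result is algebraic and needs no assumption beyond such units not being hospital. Only the home-based rule is consistent with the article's own account of what the outcome captures, so it is the formula that should change.

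The size of the effect on the mean is not known. The figure of 1.4–3.5 days rests on an assumed 10–25% of participants spending 14 days in such settings, and the article gives neither number. DAOH-90 is exposed to the same ambiguity. The point is worth correcting because this outcome is proposed as the definitive trial's primary measure and its distribution is a main planning product of the study.

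**What to change.** Restate the formula as 30 minus all days from randomisation not spent at home or usual residence, counting the index stay, readmissions, community rehabilitation and any other temporary care, with 0 for death by day 30. Apply the same rule to DAOH-90, with 90 in place of 30.

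Confirm that the case report form and the 30- and 90-day contacts record the date of each change of setting, including arrival home and any readmission. Add those dates if they do not. The check is worth making because Data management describes data being collected up to hospital discharge, whereas the home-based rule needs dates after it. A hospital-only summary alongside is optional.

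The cost is one reworded sentence and, at most, a few date fields. Mean DAOH will be lower than under the literal formula, by an amount that depends on the unknown use of rehabilitation beds. The rule should be settled before any DAOH data are summarised.
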